### Outcomes

The proportion of all-cause mortality at 30 days will be compared between the intervention and control groups. Survival data will be collected through telephone follow-up. Secondary outcomes are all-cause mortality at 365 days; use of long-term RRT; success in weaning from ECMO, defined as survival after 24 h from weaning; health-related quality of life according to scores on the EuroQoL (EQ-5D-5L) questionnaire at 365 days; length of stay at ICU and hospital; unplanned hospital readmission; and separately on cardiac and non-cardiac death.

Severe adverse events (SAEs), such as major bleeding, cardiac arrhythmias, ventilator-associated pneumonia, bloodstream infection, surgical site infection, limb ischemia from any cause, and ischemic or hematologic stroke will be collected systemically. Any other SAEs determined by the physicians through spontaneous reporting (Table 4 outlines SAE definitions). The publication will detail each documented SAE. All the SAEs will be coded through MedDRA.

**Table 4 Tab4:** Definition of SAEs

The SAEs include but are not limited to	
Major bleeding	
Bleeding requires transfusion for > 2 units	
Severe arrhythmias	
Type II second-degree AVB or third-degree AVB	
Sustained ventricular tachycardia (> 30 s)	
Ventricular fibrillation	
Ventilator associated pneumonia, which needs to meet all the criteria below:	
At least 48 h after endotracheal intubation	
Chest X-ray showing sustained or worsening shadowing (infiltrates or consolidations)	
Signs of pulmonary consolidation and/or crackles on auscultation, at least meet one of the following criteria:	
a) White blood cell count > 10 × 10^9^/L or < 4 × 10^9^/L	
b) Temperature > 37.5 °C, purulent secretions	
c) Positive cultures obtained directly from bronchial secretions	
Bloodstream infection	
Positive cultures obtained from the peripheral blood	
SSI	
Purulent drainage in the operated region with pain or tenderness, localized swelling, redness, and heat or fever, requiring operation, including superficial incisional wound SSI, deep incisional wound SSI, and organ/space SSI	
Limb ischemia from any cause	
Physical examination demonstrating pain, pallor, pulseless, cold, and motor or sensor deficit	
Requiring decannulation of ECMO catheter or surgical intervention	
Stroke	
New onset abnormal neurological signs and symptoms last for at least 24 h with radiographic evidence	
Any other severe adverse events determined by the physicians	

*AVB* atrioventricular block, *ECMO* extracorporeal membrane oxygenation, *SAE* serious adverse events, *SSI* surgical site infection

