## Methods

### Study design (Fig. 1)

ELITE is a prospective, multi-center, open-label, randomized controlled trial, with a 2 × 2 partial factorial design to evaluate whether early CRRT support and beta-blockade will reduce 30-day mortality in a broad range of ECMO patients admitted to hospitals in China from July 2018. In arm A, patients are randomized to early CRRT within 24 h of initiation of ECMO or to control, regardless of whether there is a conventional indication, or to the control where patients only receive CRRT according to a conventional indication. In arm B, patients are randomized to the intravenous esmolol group or usual care. The trial design and protocol adhere to the Recommendations for Interventional Trials (SPIRIT) criteria [19] (Table 1) and checklist in Table 5 in Appendix. The study is planned to enroll patients from 10 centers in China (see Table 5 in Appendix for the hospital list).

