### Trial status

There have been 89 patients enrolled at 10 hospitals in study A, and the enrollment is still ongoing. However, study B was stopped in August 2019 in the absence of any patients being enrolled. Although we aimed to test the hypothesis that beta-blockers would protect the myocardium in ECMO patients, we found this too challenging to undertake as these patients have low BP, which is a contraindication to such treatment and raised concerns of harm among investigators. Moreover, the short time window for enrollment was another barrier to recruitment, and by the time a patient is stable and without vasopressors, it is near the time to wean them off ECMO. Consequently, we decided to close recruitment into arm B. During the COVID pandemic, patient enrollment has become more challenging. A review of the feasibility of the trial will be made by the Steering Committee at the end of 2022.

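### Serious CRRT-specific events are not on the systematically collected SAE list and rest on spontaneous open-label reports, so the comparison of these residual events (not of all harms) is open to reporting bias

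*Protocol article*

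**What the plan says.** The Outcomes section of the protocol article describes two routes by which SAEs reach the database.

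- **Systematic route.** It names "Severe adverse events (SAEs), such as major bleeding, cardiac arrhythmias, ventilator-associated pneumonia, bloodstream infection, surgical site infection, limb ischemia from any cause", and ends the list with "ischemic or hematologic stroke will be collected systemically". I read the last word as systematically. That makes seven categories.
- **Spontaneous route.** It then adds "Any other SAEs determined by the physicians through spontaneous reporting".

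Table 4 opens with "The SAEs include but are not limited to", defines each of the seven categories, and closes with a physician-determined catch-all. Major bleeding is defined as "Bleeding requires transfusion for > 2 units", and bloodstream infection by a positive peripheral blood culture. Severe arrhythmias comprise "Type II second-degree AVB or third-degree AVB", sustained ventricular tachycardia and ventricular fibrillation. No item is specific to CRRT.

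The Study design section calls ELITE an "open-label, randomized controlled trial". The Trial status section reports that "study B was stopped in August 2019" with no patient enrolled, and that study A continues with 89 patients.

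**The concern.** Table 2 excludes patients who already have a conventional CRRT indication, and the early group receives CRRT whether or not one develops. Harm from the procedure is therefore a main counterweight to any benefit, and it should be measured by a rule that works the same way in both groups.

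Under the stated rule, a serious CRRT-specific event outside the seven categories enters the data only if a physician who knows the allocation decides to report it. Staff running CRRT may notice and report such events more readily. Equally, they may regard them as expected and not report them. Either way, the reporting fraction can differ between groups. The Statistical analysis section compares categorical safety endpoints by chi-square. Blinding the statisticians cannot correct selection that took place at the bedside. The DMC, which meets every 6 months and is told of adverse events, would see the same data.

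**Working it through.** **1. Where each type of harm falls under the stated rule**

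| Harm | Route in Outcomes / Table 4 | Other data in both groups |
|---|---|---|
| Fatal harm of any cause | Mortality at 30 and 365 days | – |
| Major bleeding | Systematic, defined | Hemoglobin, platelets (Table 1) |
| Bloodstream infection | Systematic, defined | Temperature, white cells (Table 1) |
| VT / VF, possibly from electrolyte shifts | Systematic, defined | K, Na (Table 1) |
| Hypotension on CRRT | Not named: spontaneous | Blood pressure (Table 1) |
| Electrolyte disturbance | Not named: spontaneous | K, Na (Table 1) |
| Thrombocytopenia | Not named: spontaneous | Platelets (Table 1) |
| Dialysis-access or circuit complication | Not named: spontaneous | None |

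The Table 1 values are taken at randomization, Day 3 and Day 7. Early CRRT starts within 24 h of ECMO and has a stated minimum of 12 h, so a brief event can fall between measurements. The exposed set is the last four rows, and only events that reach SAE severity.

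**2. How much unequal reporting could matter (illustration only)**

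The documents give no SAE rate and no reporting rate, so there is no plan figure to reproduce. Every rate below is an assumption. The group size is the planned 248.

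Let the true risk be p in both groups, with fractions r_E and r_C of events reported. Observed risks are a = p·r_E and b = p·r_C, and the apparent risk ratio is r_E / r_C. With m = (a + b)/2, the chance of a significant result in the direction of the bias, at two-sided 5%, is

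Φ{ [ |a − b|·√n − 1.96·√(2m(1 − m)) ] / √(a(1 − a) + b(1 − b)) }.

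Example: p = 0.10, r_E = 0.90, r_C = 0.60. Then a = 0.09, b = 0.06 and m = 0.075. The argument is (0.03 × 15.748 − 1.96 × 0.3725)/0.3719 = −0.69, so the chance is 0.24.

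| True risk, both groups | Reported 90% vs 75% (apparent RR 1.2) | Reported 90% vs 60% (apparent RR 1.5) |
|---|---|---|
| 5% | 0.06 | 0.14 |
| 10% | 0.09 | 0.24 |
| 20% | 0.14 | 0.46 |

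With equal reporting the figure would be 0.025 in that direction. Reversing the fractions (60% early, 90% control) gives an apparent risk ratio of 0.67 and the same chances of a false deficit.

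A second set of assumptions, with a true risk of 15% in both groups:
- 80% vs 50% reported: 0.12 vs 0.075, chance 0.39.
- 65% vs 50% reported: 0.0975 vs 0.075, chance 0.14.

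**3. Loss of power when reporting is low but equal (same formula)**

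True risks of 20% vs 10%, fully captured, give power 0.88. With half the events reported in each group the observed risks are 10% vs 5%, and power is 0.56.

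**4. Limit of the illustration**

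Step 2 assumes equal true risk, which is sensible only for events that can occur in either group (hypotension, electrolyte disturbance, thrombocytopenia). Access and circuit complications cannot occur in a control patient who never receives CRRT, so a test of equal proportions is not a meaningful question for them.

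**The case against.** The strongest reply has four parts.

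- **The systematic list is introduced by examples, and Table 4 is open-ended.** On this view nothing assigns CRRT events to the weaker route. This does not stand: the sentence that follows sends all other SAEs to spontaneous reporting, so an unnamed event goes there. An open list only widens that route.
- **The article condenses a fuller protocol and case report form, which may solicit more events.** This stands as a limit on certainty. The article does, however, state a collection rule and print the definitions, so the point rests on what is written and not on a missing list.
- **Much harm is already covered.** This stands. A reader might infer that no CRRT harm is collected systematically, or that harm of early CRRT cannot be compared fairly at all. The documents do not support either. Bleeding and bloodstream infection can be CRRT harms and are collected by one definition in both groups, mortality does not depend on SAE reporting, and Table 1 gives scheduled values in both groups. The lack of blinding is acknowledged in the Discussion, and the DMC includes a nephrologist and a critical care physician.
- **Not every hypotensive episode, electrolyte shift or circuit problem is an SAE.** This stands, and limits the fix to serious events.

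A reader might also take the high-grade AV block item, kept after study B closed, as a flaw. It is a general arrhythmia event, was set for a trial with two questions, and does not disturb the CRRT comparison.

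**Conclusion.** The point holds in a limited form. As written, serious CRRT-specific events outside the seven categories depend on spontaneous reports by unblinded physicians, and their comparison between groups can be biased in either direction. The comparisons of mortality and of the listed SAEs do not share this weakness.

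The size cannot be derived from the documents. The 6% to 46% range for a falsely significant excess, and the fall in power from 0.88 to 0.56, show what assumed rates would do with 248 per group; they do not estimate what will happen in ELITE. They also presume full enrollment, whereas 89 patients had been enrolled and a feasibility review was pending. The conclusion rests on the article's collection rule being the one in force. A case report form that already solicits these events in both groups would settle the matter.

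**What to change.** Amend the Outcomes section and Table 4 as follows.

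1. Add a short, predefined set of serious CRRT-related events to the systematically collected list.
2. Apply the same definitions and one fixed window from randomization in both groups, including control patients who later receive CRRT.
3. Use the blood pressure, K, Na and platelet values already scheduled in Table 1 as supporting data, without relying on them alone.
4. Tabulate solicited and spontaneous events separately.
5. Describe events that can occur only on CRRT (access, circuit) by group, with the number exposed, and do not test them as if both groups were equally exposed.

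The AV block item can stay. If the full protocol or case report form already does this, a sentence saying so is enough.

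The cost is a few more fields for sites, and chart review or separate reporting for the 89 patients already enrolled. Against the target of 496, 496 − 89 = 407 patients were still to be recruited, so most of the planned data could be collected under the new rule. Treatment, the primary outcome and the sample size are unchanged.

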### Eligibility

The broad inclusion criteria are used for both arms, whereby adult patients who have received ECMO for any reason within 24 h and 7 days, for arms A and arm B, respectively, are eligible (Tables 2 and 3). Patients are excluded from arms A and B if they had a definite indication or contraindication to either CRRT or beta-blockers, respectively. As ECMO is often initiated by a specialist team to rescue and transfer patients to larger hospitals in China, a timeframe of 24 h after ECMO implantation was used for early CRRT in arm A, while a relatively stable hemodynamic status (dopamine/dobutamine < 5 μg/kg/min, with no administration of adrenaline or norepinephrine) and within 7 days after initiation of ECMO was required for eligibility into arm B. Identification of potentially eligible patients is the responsibility of the ECMO team in participating centers. After ECMO implantation or when the patient is transferred to the participating center, eligibility for study arm A will be assessed. Prior to 7 days after ECMO implantation, when patients are stable on ECMO, eligibility for study arm B will be assessed.

**Table 2 Tab2:** Inclusion and exclusion criteria for study A

Inclusion criteria	
Patients receiving VA-ECMO for any reason within 24 h	
Provision of informed consent	
Exclusion criteria	
Age < 18 years	
Receiving ECMO bridging to heart transplantation	
With convention indication of CRRT: AKI prior to enrollment caused by any reason, at least one of the following criteria is met:	
Severe hyperkalemia (> 6.5 mmol/L)	
Metabolic acidosis (pH < 7.2)	
Pulmonary edema	
Blood urea nitrogen level > 112 mg/dL	
Oliguria (urine output < 200 mL/12 h) for more than 72 h	
CKD, with estimated GFR<30 mL/min	
Have already initiated CRRT	
Active hemorrhage/thrombotic thrombocytopenic purpura	
Receiving ECMO again during hospitalization or respiratory failure has already initiated VV-ECMO or extracorporeal carbon dioxide removal device before the initiation of VA-ECMO of this time	

*AKI* chronic kidney disease, *CKD* chronic kidney disease, *CRRT* continuous renal replacement therapy, *ECMO* extracorporeal membrane oxygenation, *GFR* glomerular filtration rate, *VA-ECMO* veno-arterial extracorporeal membrane oxygenation, *VV-ECMO* veno-venous extracorporeal membrane oxygenation

**Table 3 Tab3:** Inclusion and exclusion criteria for study B

Inclusion criteria	
Patients receiving VA-ECMO for any reason	

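### Table 4 defines bloodstream infection by positive peripheral cultures alone, so a skin contaminant counts as an event and weakens the between-group comparison of this safety outcome

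*Protocol article*

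**What the plan says.** The Outcomes section of the protocol article names seven kinds of severe adverse event for active collection, among them "bloodstream infection, surgical site infection, limb ischemia from any cause, and ischemic or hematologic stroke will be collected systemically". It refers to Table 4 for their definitions. The whole entry for bloodstream infection there is "Positive cultures obtained from the peripheral blood".

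Other rows of Table 4 are tighter:

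- Ventilator-associated pneumonia is introduced by "Ventilator associated pneumonia, which needs to meet all the criteria below". The first condition is "At least 48 h after endotracheal intubation", followed by imaging and clinical findings. A positive bronchial culture is only one of three alternatives within the last condition.
- Surgical site infection needs purulent drainage with local signs or fever, and an operation.
- Stroke is "New onset abnormal neurological signs and symptoms last for at least 24 h with radiographic evidence".

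Three other places matter. Table 2 admits "Patients receiving VA-ECMO for any reason within 24 h" and lists no exclusion for existing infection. Table 1 records SAEs at days 3, 7, 30 and 365 and schedules no blood cultures. The Study design section states that "ELITE is a prospective, multi-center, open-label, randomized controlled trial". Bloodstream infection is neither the primary nor a secondary outcome.

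**The concern.** The printed rule is an operative definition, and it admits events that are not infections. Take three records:

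- (a) One culture set grows a common skin commensal in a patient without signs of infection.
- (b) A patient known to be bacteraemic before randomization has a further positive culture the next day.
- (c) A recognised pathogen grows for the first time after randomization.

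Taken literally, the line counts all three. Only (c) is clearly the event that the row's title describes.

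Case (a) matters more, because the chance of at least one contaminated set rises with every set drawn. Table 1 schedules no blood cultures, so the number drawn presumably rests with treating staff, who know the allocation. Two errors can follow. Equal contamination in both groups dilutes the risk ratio and costs power to see a real excess. Unequal culturing can produce an excess by itself. Safety endpoints are to be compared between groups by chi-square test (Statistical analysis section), so either error would reach the published comparison.

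**Working it through.** **Inputs.** From the documents: 248 per group (Sample size), 1:1 allocation (Randomization), two-sided 5% (Statistical analysis). The documents give no infection rate, contamination rate or number of cultures per patient, so there is no figure of the plan's own to reproduce. Assumed: a fraction c = 1%, 2% or 3% of sets is contaminated, independently; n = 2, 4 or 6 sets per patient; true risk 10% in controls and 15% or 20% with early CRRT.

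**Formulas.**
- False event per patient: f = 1 − (1 − c)^n.
- Observed risk: 1 − (1 − true risk)(1 − f).
- Power: Φ[(d − 1.96·SE0)/SE1], where d is the difference in observed risks, SE0 the pooled and SE1 the unpooled standard error.

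**Without false events.** For 10% vs 20%: d = 0.100, SE0 = 0.0321, SE1 = 0.0318. Then (0.100 − 0.0628)/0.0318 = 1.17, and power is 88%. For 10% vs 15%, power is only 39%.

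**Equal contamination in both groups.**

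| c | n | f | Observed ratio, true 10% vs 15% | Power, true 10% vs 20% |
|---|---|---|---|---|
| 1% | 2 | 2.0% | 1.42 | 84% |
| 1% | 4 | 3.9% | 1.35 | 79% |
| 1% | 6 | 5.9% | 1.31 | 75% |
| 2% | 2 | 4.0% | 1.35 | 79% |
| 2% | 4 | 7.8% | 1.27 | 71% |
| 2% | 6 | 11.4% | 1.22 | 63% |
| 3% | 2 | 5.9% | 1.31 | 75% |
| 3% | 4 | 11.5% | 1.22 | 63% |
| 3% | 6 | 16.7% | 1.17 | 53% |

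Worked example, last row: f = 1 − 0.97^6 = 0.167. Observed risks for 10% vs 15% are 1 − 0.90 × 0.833 = 0.250 and 1 − 0.85 × 0.833 = 0.292, a ratio of 1.17. For 10% vs 20% they are 0.250 and 0.334, so d = 0.0833, SE0 = 0.0408 and SE1 = 0.0407. Then (0.0833 − 0.0800)/0.0407 = 0.08, and power is 53%.

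The risk difference is multiplied by (1 − f), so it moves less than the ratio: a true 5.0 points is seen as 4.9 points (f = 2.0%) down to 4.2 points (f = 16.7%).

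**Unequal culturing, no true effect.** With a true risk of 10% in both groups, 4 sets per patient in one and 6 in the other, the spurious excess is 0.90 × (f at n = 6 − f at n = 4):
- c = 1%: 0.90 × (0.0585 − 0.0394) = 1.7 points
- c = 2%: 0.90 × (0.1142 − 0.0776) = 3.3 points
- c = 3%: 0.90 × (0.1670 − 0.1147) = 4.7 points

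**The case against.** **Importance.** A reader might infer that the wording blurs a main harm of early CRRT. The article does not say that. It lists bloodstream infection as one of seven systematically collected events, and 30-day mortality is untouched. This limits the weight of the point.

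**Prior bacteraemia.** A reader might also infer that infection present at randomization biases the comparison. The documents do not support that. The row sits in a table of adverse events, SAEs are collected only after randomization, and 1:1 allocation should balance prior bacteraemia, leaving noise. That stroke alone is called new onset proves little, since the bleeding, arrhythmia and limb ischaemia rows carry no such word either. What remains is that a persisting positive culture at day 3 or 7 still fits the line.

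**Plural wording.** The entry says cultures, not a single culture. But a plural is not a two-set rule, and the pneumonia row uses the same plural for bronchial secretions.

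**Assumed inputs.** This stands in full. The mildest case costs about 4 points of power. The spurious excess needs one group to be cultured 50% more often, for which the article gives no evidence. Enrolment is the larger limit: at the reported 89 patients, about 45 per group, power for 10% vs 20% is 26% even with a perfect definition.

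**Merit of a laboratory-only rule.** It needs little judgement, which is an advantage in an open-label trial. This also stands, and it argues against adding a bedside judgement of clinical signs.

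**Condensed article.** Case-report-form fields may well exist in the full protocol, and their absence here is no finding. The definition itself, however, is printed.

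**Conclusion.** The point holds as a badly fixed definition of one safety event. Applied as printed, the Table 4 line counts contaminants as bloodstream infections, unlike the pneumonia and surgical-site rows, which require clinical findings. Equal misclassification pulls the risk ratio towards 1; unequal culturing could push it either way. Over the assumed range the loss runs from slight to substantial, but no single value in it can be called likely from the documents. The article supports neither a claim that the primary result is affected nor a claim that the groups are in fact cultured differently. The change is worth making because it is cheap and recruitment into study A was reported as ongoing, with 89 of 496 patients enrolled.

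**What to change.** Reword the Table 4 row so that a bloodstream infection is an event with onset after randomization in which either a recognised pathogen grows in at least one peripheral blood culture, or the same common skin commensal grows in at least two separately drawn cultures. An organism already grown before randomization does not count.

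Record the organism, the number of positive cultures and the culture status before randomization. Classify all events, including those of patients already enrolled, from microbiology reports by someone unaware of allocation. This keeps the rule laboratory-based and stops reclassification from adding bias of its own.

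The cost is one row of Table 4, three data fields where they are not already held, and re-reading the culture reports of enrolled patients. Somewhat fewer events will be counted. The rule reduces but does not remove the effect of unequal culturing, because more cultures also find more true infections and more repeated commensals.

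### Table 4 lets some intracranial haemorrhages miss both the stroke and the major-bleeding definitions and depend on spontaneous reporting in an open-label trial

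*Protocol article*

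**What the plan says.** The rules stand in the Outcomes section of the protocol article and its Table 4.

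- Stroke: "New onset abnormal neurological signs and symptoms last for at least 24 h with radiographic evidence". Duration and imaging are both required. No provision covers death before 24 h or signs that cannot be observed.
- Major bleeding: "Bleeding requires transfusion for > 2 units". This is the only criterion. Site and fatal outcome play no part.
- The table is open at both ends. It is headed "The SAEs include but are not limited to" and closes with "Any other severe adverse events determined by the physicians".
- The text sets two routes of capture. For the named events, the list ends "ischemic or hematologic stroke will be collected systemically" (read here as haemorrhagic stroke and systematic collection). The second route is "Any other SAEs determined by the physicians through spontaneous reporting".
- On reporting: "The publication will detail each documented SAE". All SAEs are coded in MedDRA.

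The Study design section describes the trial as open-label.

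**The concern.** Intracranial haemorrhage can be fatal within hours, and its signs can be hidden in a sedated patient. Both situations are foreseeable here. The Sample size section assumes 70% control mortality at 30 days. Table 1 records mechanical ventilation at randomization and at days 3, 7 and 30, and ventilator-associated pneumonia is a named SAE.

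Stroke and major bleeding are the two named categories in which such an event belongs. If it meets neither definition, it moves from systematic collection to reports made at the discretion of physicians who know the allocation. A shortfall that is equal in both groups makes a real harm harder to see. An unequal shortfall biases the comparison, in a direction that cannot be predicted. In study A the early group receives CRRT without waiting for a conventional indication, so dependable harm counts are needed to judge the strategy.

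**Working it through.** The point turns on the wording of two definitions. The plan gives no figure for it, so there is nothing to reproduce.

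**Step 1. Apply both definitions to an intracranial haemorrhage seen on imaging.**

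| Course of the event | Units needed | Stroke? | Major bleeding? |
|---|---|---|---|
| Signs last 24 h or more | 2 or fewer | Yes | No |
| Signs last 24 h or more | More than 2 | Yes | Yes |
| Signs, then death before 24 h | More than 2 | No (duration) | Yes |
| Signs, then death before 24 h | 2 or fewer | No (duration) | No |
| No detectable signs under sedation | More than 2 | No (signs) | Yes |
| No detectable signs under sedation | 2 or fewer | No (signs) | No |

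Two of the six rows meet neither definition. Both need a combination: failure of the stroke rule together with 2 units or fewer. A bleed found only at autopsy also fails the stroke rule, because radiographic evidence is required.

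**Step 2. Follow those two rows through the rest of the section.** The open list and the closing entry admit them as SAEs. Once documented, they are coded and published. If the patient dies by day 30, the death counts in the primary outcome. What changes is the category in which the event is counted and the way it is found.

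**Step 3. Can the size be computed?** That would need the rate of intracranial haemorrhage in each group, the share failing both definitions, and the share of those recovered by spontaneous report. The documents give none of these. The mortality assumptions (70%, and 0.70 × (1 − 0.20) = 56%) do not supply them either, because they say nothing about death within 24 h of a bleed.

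**Step 4. Illustration with assumed rates only.** Suppose the true rates were 5% and 10%, with the planned 248 per group, and let m be the share missing from the named counts. The counted rates are then p₁ = 0.05(1 − m) and p₂ = 0.10(1 − m). With p̄ their mean and d = p₂ − p₁, at two-sided 5%:

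power = Φ{[d√n − 1.96√(2p̄(1 − p̄))] / √(p₁(1 − p₁) + p₂(1 − p₂))}

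- m = 0: (0.05 × 15.748 − 1.96 × 0.3725)/0.3708 = 0.155, power 56%.
- m = 0.25: rates 3.75% and 7.5%, power 44%.
- m = 0.50: (0.025 × 15.748 − 1.96 × 0.2687)/0.2681 = −0.496, power 31%.

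Expected events are (0.05 + 0.10) × 248 = 37.2, of which 9.3 (m = 0.25) or 18.6 (m = 0.50) would be missing from the named counts. Here m must be the share failing both definitions; the share failing the stroke rule alone is larger. The calculation shows direction only. It is not an estimate for this trial.

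**The case against.** A reader might infer that these bleeds drop out of the safety comparison altogether. The documents do not support that. The SAE list is open, physicians may report any other event, each documented SAE is to be published and coded so that it can be tabulated by group, and a fatal bleed by day 30 is a primary-outcome event. A reader might also infer that every intracranial bleed in a sedated or dying patient escapes both categories. That is too absolute: some sedated patients will show signs for 24 h, and some will need more than 2 units.

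Further points on the other side:

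- *Sites are asked about haemorrhagic stroke.* This stands in part, because the question may prompt a report. Whether the event counts as stroke is still settled by Table 4.
- *High mortality does not show that death within 24 h of a bleed is common.* This stands. So does the point that the study A exclusion, "Active hemorrhage/thrombotic thrombocytopenic purpura", does not bear on how later events are defined.
- *Any power figure is built on assumed rates.* This stands. Even with complete capture, the illustration has only 56% power.
- *Imaging-only events bring a bias of their own.* This stands. Table 1 schedules no brain imaging, so finding silent lesions depends on unblinded decisions to scan. It argues against adding imaging-only infarct to the stroke definition.
- *A condensed article may leave such detail to the full protocol or CRF instructions.* This has limited force. Table 4 is presented as the definition and states closed criteria for these two events. If the fuller documents already cover the gap, only the article needs aligning.

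The secondary split into cardiac and non-cardiac death does not fill the gap, since a non-cardiac death is not identified as a bleed.

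**Conclusion.** The gap is real but limited. Read literally, Table 4 places an intracranial haemorrhage outside both named categories when it is fatal before 24 h or without detectable signs, and also needs 2 units or fewer. Its capture then rests on spontaneous reporting in an open-label trial, so the stroke and major-bleeding counts can be too low and may be affected unequally by group. Such events remain within the SAE data if reported, and the 30-day mortality result is untouched.

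The size cannot be derived from the documents. The conclusion rests on reading the two definitions as written and on taking the named events to be collected systematically. It is a moderate weakness in ascertainment that a cheap change of wording can reduce.

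**What to change.** In Table 4:

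1. Stroke: require new neurological signs lasting at least 24 h, or until death if sooner, still with radiographic evidence.
2. Major bleeding: keep the present rule of more than 2 units, and add fatal bleeding and imaging- or autopsy-confirmed intracranial haemorrhage, each regardless of units transfused.
3. Do not add imaging-only infarct to the stroke definition. If it is wanted, report it separately.

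Costs: the CRF wording changes. SAEs in the 89 patients already enrolled in study A must be reclassified so that two definitions are not mixed. Reported event rates become slightly higher. No additional scans are needed. One limitation remains: finding an intracranial haemorrhage without signs will still depend on unscheduled, unblinded imaging, and the report should say so.
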